Other studies have described a protocol for ex vivo angiography of the fetal vessels, including Link et al [16] and Chen et al [17]. The described technique allows for imaging of the architecture of the whole fresh human placental vascular tree by injection of oil in the umbilical cord vessels. This protocol can reveal up to the sixth level of placental vascularization at a submillimeter quasi-isotropic resolution [17]. Link et al [16] recently compared IUGR and normal placental vascular trees using ex vivo angiography [16]. The main limitation of this work is that the understanding of placental structure and vasculature at different gestational stages is limited [18,19].

The main objective of our study is to compare the vascular architecture of the placenta in normal and pathological pregnancies; for example, PE and intrauterine growth restriction. Our secondary objectives are to (1) compare texture features on MRI between groups (normal and pathological), (2) quantitatively compare the vascular architecture between both pathological groups (pathological IUGR and pathological PE), (3) evaluate the quality of the histological examination in injected placentas, and (4) compare vascularization indices to histological analysis.

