### MR Image Analysis

All the placental data will be archived and managed by a local research image management system ArchiMed. A MATLAB program has already been developed to segment the acquired placenta data and extract the vessel tree structure [17]. Owing to the good contrast-to-noise ratio and signal-to-noise ratio of the MR images, a simple thresholding is sufficient to delineate the vessel tree. A fast-marching algorithm will be used to quantitatively characterize the placenta’s vessel tree. Separation of the artery and vein tree structure will be achieved with a homemade software written in C++ as described by Kerrien et al [24]; the segmented placenta vessel data will be rendered in 3D, and its skeleton will be overlapped with its 3D model using this software. Morphological parameters including total vessel density, artery and vein density (per cm^3^), and tortuosity and bifurcation density (per cm^3^) will be calculated automatically or semiautomatically. Total vessel density is defined as the overall vessel density regardless of whether the vessel is an artery or vein. It is calculated as the vessel voxel volume divided by the whole placenta volume, while artery and vein vessel density are defined as artery and vein volume divided by whole placenta volume, respectively. The 3-vessel density will be calculated automatically by the software. Calculation of tortuosity and bifurcation density are computed semiautomatically as the branching of the vessel network and bifurcations need to be checked by observers. Tortuosity is defined as the curvilinear distance and Euclidean distance between the starting and the end of a vessel path (in this case, a vessel branch) [24]. Bifurcation density is defined as the number of detected bifurcations divided by the placental volume. Radiomics features, as described by Vallières et al [25], will also be extracted to quantify the differences among the 3 groups of placentas [25]. The quantitative parameters will be described by their mean (SD), median, maximum and minimum, and n (%) values. Mean values between groups will be compared using the Student *t* test or Mann-Whitney test, unpaired in accordance with whether the data are normally distributed, depending the type of data. Linear regression models will be used to test the group and the effect of gestational age on the parameters considered.

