### Outcomes

The primary outcome will be the vascular architecture, described by vascularization indices (total vascular density, arterial and venous density in cm^3^, tortuosity index, and branching index) measured from ex vivo MRI in both groups (physiology and pathology).

The secondary outcome measures are the following:

Secondary objective 1: measurement of texture indices as established by Vallières et al [25].Secondary objective 2: measurement of vascularization indices and texture based on the participant group.Secondary objective 3: number of placentas with an appropriate histological quality to be examined microscopically.Secondary objective 4: statistical comparison between vascularization indices achieved through MRI and histological evaluation (presence or absence of FVM, presence of absence of MVM, if present: grading of the lesions).

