### Sample Size Consideration

Given the exploratory nature of this study and in the absence of data allowing for sample size estimation, we consider it necessary to include 100 women: 40 women with a normal pregnancy and 60 women with a pathological pregnancy (30 women with an IUGR and 30 with PE).

In fact, to obtain a sufficiently precise characterization and to be able to use descriptive statistics applicable to large samples (mean, SD values), we will need to obtain at least 30 observations in each group.

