### Statistical Analysis

Quantitative data will be described by their mean (SD), median, and maximum and minimum values. Qualitative data will be expressed as n (%) values. Between-group comparisons will be performed using the Student *t* test or the Mann-Whitney test, matched or unmatched, depending on the type of data. The chi-square test or the Fisher exact test will be used to compare the qualitative data between groups. The analyses will be performed with R software (R Foundation for Statistical Computing). No intermediary analysis is intended. The analyses will be performed on a per-protocol basis.

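### The Student t test is named for groups of 40 and 60; if spreads differ it misses its 5% level, and Welch's test corrects this without loss against Student

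*Protocol article*

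**What the plan says.** The protocol article describes the group comparisons in two places.

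- MR Image Analysis: "Mean values between groups will be compared using the Student" t test or the Mann-Whitney test, "unpaired in accordance with whether the data are normally distributed". The section adds a model-based analysis: "Linear regression models will be used to test the group and the effect of gestational age on the parameters considered".
- Statistical Analysis: "Between-group comparisons will be performed using the Student" t test or the Mann-Whitney test, this time "matched or unmatched, depending on the type of data". Normality is not mentioned here.

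The Outcomes section defines the primary outcome as vascularization indices "measured from ex vivo MRI in both groups (physiology and pathology"). Sample Size Consideration sets the numbers: "40 women with a normal pregnancy and 60 women with a pathological pregnancy (30 women with an IUGR and 30 with PE"). A secondary objective is to "quantitatively compare the vascular architecture between both pathological groups (pathological IUGR and pathological PE").

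Neither section mentions equal or unequal variances. The article gives no standard deviation, significance level or power.

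**The concern.** By its usual meaning, the Student t test estimates one common variance from both groups. When group sizes differ, the pooled estimate is dominated by the larger group. If that group is also the more variable, the standard error is too large: the test is conservative and loses power. If the smaller group is the more variable, the standard error is too small and false positives exceed the nominal rate. The primary comparison, 40 against 60, is exposed in either direction.

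The planned regression shares the weakness. With a two-level group term alone, ordinary least squares gives exactly the pooled t test, and adding gestational age does not remove the equal-variance assumption.

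Two wording problems sit alongside. The two sections give different rules for choosing the test. The first also describes both tests as comparing mean values, which Mann-Whitney does not do.

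**Working it through.** **Inputs from the article.** 40 normal, 30 IUGR and 30 PE; 40 + 30 + 30 = 100, as stated. The primary comparison is 40 v 60 and the comparison between diseases is 30 v 30. There is no stated error rate or power to reproduce.

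**Assumed.** Two-sided 5% level, normal data, and an SD ratio r (pathological/normal) from 0.5 to 2, with the normal SD set to 1.

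**Formula.** The variance that the pooled test attributes to the mean difference is on average A = s²(1/40 + 1/60), where s² = (39 + 59r²)/98. The true variance is B = 1/40 + r²/60. With k = √(A/B), the large-sample error is 2[1 − Φ(1.96k)].

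**Example, r = 2.** s² = (39 + 236)/98 = 2.806. A = 2.806 × 0.04167 = 0.1169. B = 0.0250 + 0.0667 = 0.0917. k = √1.2755 = 1.129. Error = 2[1 − Φ(2.214)] = 2.7%.

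**Results for 40 v 60.** Simulation used 200,000 trials per row; power is for a true difference of 2.85 standard errors.

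| r | k | Student error, formula | Student error, simulated | Welch error, simulated | Power, Student / Welch |
|---|---|---|---|---|---|
| 0.5 | 0.885 | 8.3% | 8.4% | 5.0% | not comparable |
| 0.67 | 0.925 | 7.0% | 7.0% | 5.0% | not comparable |
| 0.8 | 0.957 | 6.1% | 6.1% | 5.1% | not comparable |
| 1 | 1.000 | 5.0% | 5.0% | 5.0% | 80.6% / 80.5% |
| 1.25 | 1.045 | 4.0% | 4.1% | 5.0% | 77.9% / 80.4% |
| 1.5 | 1.081 | 3.4% | 3.5% | 5.0% | 75.8% / 80.5% |
| 2 | 1.129 | 2.7% | 2.7% | 4.9% | 72.8% / 80.7% |

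Power is not compared for r below 1 because Student exceeds its level there. For r = 1.25, 1.5 and 2 the losses are 2.5, 4.7 and 7.9 points. At r = 1 the two tests differ by about 0.1 point.

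**30 v 30.** With equal sizes n, the pooled variance of the difference is [(s₁² + s₂²)/2] × (2/n) = (s₁² + s₂²)/n, which is Welch's. So k = 1 at every ratio, and simulated Student error stays at 5.0% to 5.3%.

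**Mann-Whitney read as a test of means.** A two-stage rule was simulated for 40 v 60 with equal means (8,000 trials per setting): Shapiro-Wilk at 5% in each group, then Student or Mann-Whitney. At SD ratios of 0.5 and 2 it rejected in 14.5% and 9.8% of trials with gamma data (shape 4), and in 22.0% and 17.7% with lognormal data (sigma 0.5). With equal SDs it rejected in 4.8% and 5.2%. The excess comes almost entirely from the Mann-Whitney branch. It shows that a Mann-Whitney rejection need not mean that the means differ.

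**The case against.** **Equal variance is inferred from the name.** The article never says that variances are pooled. The analyses will run in R, where the unequal-variance form is available and is the default. A separate analysis plan may settle the option. This stands as far as it goes, but Student is the test the article names, twice, and correcting the name removes the doubt.

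**Unequal spread is assumed.** This stands. At ratios between 0.8 and 1.25 the error is only about 4% to 6%, which matters little in an exploratory pilot. Nothing in the article shows the ratio to be more extreme.

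**A reader might infer inflated false positives in the primary comparison.** The article does not support that. The most natural reason to expect unequal spread is that the pathological group mixes two diseases, and that points to the conservative side. The effect may also be small: if the disease means differ by one within-group SD, the ratio is √(1 + 0.25) = 1.12. With the subgroups fixed at 30 each, simulated error was then 3.5% for Student and 4.0% for Welch, so Welch does not fully restore 5% in that case.

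**A reader might extend the point to normal v IUGR or normal v PE (40 v 30).** There the pattern reverses: Student's error is about 6.5% and 7.4% if the disease group's SD is 1.5 or 2 times the normal group's. But that pairwise comparison is not among the listed objectives, so it carries no weight here.

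**A reader might conclude that Welch should replace Mann-Whitney too, at no cost.** It is not free. With skewed data of equal spread at 40 v 60, Welch had 78% power against 83% for Mann-Whitney (gamma) and 78% against 91% (lognormal), a loss of 5 to 13 points. Nor does the article specify a formal normality test, so the two-stage figures above illustrate one possible reading only.

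**Conclusion.** The point holds in a limited form. For the 40 v 60 primary comparison, the named Student t test keeps its 5% level only if the two groups have equal spread. Over an assumed SD ratio of 0.5 to 2, its error ranges from about 8% down to about 3%, with 2.5 to 8 power points lost when the pathological group is the more variable. These figures rest on normal data, a two-sided 5% level and the planned numbers; the article supplies neither the SDs nor the level, so direction and size are unknown. IUGR v PE is unaffected while the analysed numbers stay equal. Welch is at least as good as Student across the range and costs nothing measurable when SDs are equal.

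The differing selection rules, and the description of Mann-Whitney as comparing means, are separate defects of wording that can be read directly from the article. Whether to keep Mann-Whitney for skewed indices is a trade-off and no part of this conclusion.

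**What to change.** - In MR Image Analysis and Statistical Analysis, name Welch's unequal-variance t test in place of Student's wherever an unpaired t test is meant. Leave the provision for matched comparisons in place.
- Use heteroscedasticity-robust standard errors in the planned regression on group and gestational age.
- Give one rule for choosing the test and state it identically in both sections, reconciling normality with type of data, and unpaired only with matched or unmatched.
- Report any Mann-Whitney result as a comparison of ranks or distributions, not of mean values.
- If an index is to be log-transformed, fix that per index in advance. Deciding it from the observed skewness would be another data-driven switch, and it changes the target to a ratio of geometric means.

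The cost is a few sentences. No extra placentas, data or software are needed, and there is no measurable loss of power against Student when SDs are equal.

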### Outcomes

The primary outcome will be the vascular architecture, described by vascularization indices (total vascular density, arterial and venous density in cm^3^, tortuosity index, and branching index) measured from ex vivo MRI in both groups (physiology and pathology).

The secondary outcome measures are the following:

Secondary objective 1: measurement of texture indices as established by Vallières et al [25].Secondary objective 2: measurement of vascularization indices and texture based on the participant group.Secondary objective 3: number of placentas with an appropriate histological quality to be examined microscopically.Secondary objective 4: statistical comparison between vascularization indices achieved through MRI and histological evaluation (presence or absence of FVM, presence of absence of MVM, if present: grading of the lesions).

### Follow-up

No specific follow-up has been planned for participants except for standard routine care. Any adverse events will be noted and reported.

### Patient and Public Involvement

Patients and the public were not involved.

### Sample Size Consideration

Given the exploratory nature of this study and in the absence of data allowing for sample size estimation, we consider it necessary to include 100 women: 40 women with a normal pregnancy and 60 women with a pathological pregnancy (30 women with an IUGR and 30 with PE).

In fact, to obtain a sufficiently precise characterization and to be able to use descriptive statistics applicable to large samples (mean, SD values), we will need to obtain at least 30 observations in each group.

### Data Collection and Management

An electronic case report file (e-CRF) will be created for each woman. The women's anonymity will be ensured by mentioning to the maximum extent possible their research code number, followed by the first letters of the last name and first name of the participant on all necessary documents or by deleting their names by appropriate means (whiteout) from the copies of source documents intended to document the study.

The MRI data will be anonymized and transferred via a secure server for storage and archiving directly in the ArchiMed database, reported to the CNIL (CNIL report number 1410005) because they cannot be transcribed in the e-CRF. The clinical data of the women are shown in Textbox 2.

### Statistical Analysis

Quantitative data will be described by their mean (SD), median, and maximum and minimum values. Qualitative data will be expressed as n (%) values. Between-group comparisons will be performed using the Student *t* test or the Mann-Whitney test, matched or unmatched, depending on the type of data. The chi-square test or the Fisher exact test will be used to compare the qualitative data between groups. The analyses will be performed with R software (R Foundation for Statistical Computing). No intermediary analysis is intended. The analyses will be performed on a per-protocol basis.

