**Methods:**

This is a prospective controlled study. We expect to include 100 placentas: 40 from normal pregnancies and 60 from pathological pregnancies (30 for IUGR and 30 for PE). Ex vivo MR image acquisition will be performed shortly after delivery and with preparation by injection of a contrast agent in the umbilical cord. The vascular architecture will be quantitatively described by vascularization indices measured from ex vivo MRI angiography data. Comparisons of vascularization indices and texture features in accordance with the group and within comparable gestational age will be also performed. After MR image acquisition, placental histopathological analysis will be performed.

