### Study Population

Enrolled women will be distributed into 3 groups (normal, IUGR, and PE) in accordance with their pregnancy status. The participants in this study are pregnant women in their third trimester in order for us to obtain comparable gestational ages between groups. Textbox 1 presents the inclusion and exclusion criteria. IUGR is defined as a birth weight less than the third percentile of the French growth curve (Association des Utilisateurs de Dossiers Informatisés en Pédiatrie, Obstétrique et Gynécologie, Lyon, France). PE is defined as a systolic blood pressure of ≥140 mm Hg and a diastolic blood pressure of ≥90 mm Hg associated with proteinuria of >300 mg per 24 hours after 20 weeks of gestation. Before inclusion, women will be informed of the aim, procedures, and predictable risks of the study (no identified clinical risk) by the investigator. Patients’ medical history, including smoking and obstetric history, will be collected. Medical information on the current pregnancy will also be collected (Textbox 2).

Inclusion and exclusion criteria.

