**Obstetric data:**
Gestational age, parity, and birth weight

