## Discussion

This study aims to evaluate whole human placental vasculature using ex vivo MRI in a normal and pathological population. We hypothesize that the placental vascular tree is altered in case of IUGR or PE compared to normal pregnancy. Our study data will provide information about uteroplacental physiology and pathophysiology by the exploration of the fetal placental side.

To our knowledge, this is the first prospective, comparative, controlled study comparing the architecture of the placental vascular tree between normal and pathological pregnancies at the same gestational age.

The groups have been selected strictly on the basis of gestational age and neonate size at birth to assess the comparison. This technique has been previously evaluated in a pilot study carried out by our team; however, only the fetal side can be analyzed with this technique.

The strength of our study is the large sample size compared to that in other studies and the control of confounding factors such as gestational age. Furthermore, our team comprises both obstetrics experts ([name]), who ensured the relevance of definitions of pathologies, and imaging experts with research engineers ([name]).

The main limitation of this study is the lack of clinical applicability of this technique. A promising recent study demonstrated the possibility to image the placental vascular tree in vivo [9]. Our results, combined with this technique, could provide to parents and obstetricians useful information during pregnancy. This trial is in accordance with the Standard Protocol Items: Recommendations for Interventional Trials checklist.

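### The plan does not fix whether an unadjusted test or the gestational-age regression answers the primary objective, and the claimed selection on gestational age has no described procedure

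*Protocol article*

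**What the plan says.** All of the following is in the protocol article.

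- **Statistical Analysis:** "Between-group comparisons will be performed using the Student *t* test or the Mann-Whitney test, matched or unmatched, depending on the type of data". No covariate or adjusted model is named there.
- **MR Image Analysis**, which defines the vascular indices: "Mean values between groups will be compared using the Student *t* test or Mann-Whitney test, unpaired in accordance with whether the data are normally distributed". It then adds: "Linear regression models will be used to test the group and the effect of gestational age on the parameters considered".
- **Abstract, Methods:** "Comparisons of vascularization indices and texture features in accordance with the group and within comparable gestational age will be also performed".
- **Study Population:** the participants are "pregnant women in their third trimester in order for us to obtain comparable gestational ages between groups". The inclusion criteria admit deliveries from beyond 25 weeks up to term, with the same limits for every group.
- **Discussion:** "The groups have been selected strictly on the basis of gestational age and neonate size at birth to assess the comparison". It also presents the comparison as one made at equal gestational age, and lists among the study's strengths "the control of confounding factors such as gestational age".
- **Data collected:** "Gestational age, parity, and birth weight", so the covariate will be available.

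The Outcomes section names the vascularization indices, compared between normal and pathological placentas, as the primary outcome. It does not say by which analysis. Trial Design calls the study nonrandomized and a pilot. Sample Size Consideration calls it exploratory and sets 40 normal and 60 pathological placentas (30 IUGR, 30 PE).

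**The concern.** The Introduction lists preterm delivery among the consequences of placental dysfunction. The document therefore gives its own reason to expect pathological placentas to be delivered earlier than normal ones. An eligibility range from beyond 25 weeks to term does not prevent such an imbalance.

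The Introduction also names limited understanding of placental vasculature at different gestational stages as the main limitation of earlier work. If the vascular indices vary with gestational age, an unadjusted comparison mixes disease with maturity. A team following the Statistical Analysis section could report such a result as the answer to the primary objective and still comply with the plan. The study would then repeat the limitation it sets out to overcome, while its Discussion states that the confounder is controlled.

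**Working it through.** **1. Passages side by side.**

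| Section | Test of groups | Gestational age |
|---|---|---|
| Statistical Analysis | t or Mann-Whitney, matched or unmatched | not mentioned |
| MR Image Analysis | t or Mann-Whitney, unpaired; then linear regression | in the regression, with group |
| Abstract, Methods | comparison by group | comparable ages, as an addition |
| Discussion | not stated | groups said to be selected on it |

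Two gaps follow. No section ranks these analyses. The matched option in one section conflicts with the unpaired tests in another, and no procedure that would create pairs is described.

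**2. The plan's own figure.** 40 + 30 + 30 = 100, and each group has at least 30, as stated. There is no power calculation to reproduce.

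**3. Illustration in weeks.** The documents give no gestational age by group, no change in any index per week and no alpha. These are all assumptions:

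- Gestational age at delivery, mean (SD): normal 39 (1.3), IUGR 36.5 (2.5), PE 35 (3) weeks. The smaller-gap setting uses IUGR 37.5 and PE 36.5 with the same SDs. Ages are held within 25.1 to 41.5 weeks.
- Index = slope × gestational age + residual with SD 1; no disease effect; two-sided alpha 0.05.

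The assumed gap between normal and pathological means is 39 − (36.5 + 35)/2 = 3.25 weeks, or 39 − (37.5 + 36.5)/2 = 2.0 weeks. The bias of the unadjusted difference is slope × gap. At 0.10 SD per week this is 0.325 or 0.20 SD, against a standard error of √(1/40 + 1/60) = 0.204 SD.

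Simulated rejection rates of the t test, with no disease effect:

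| Slope (SD per week) | Unadjusted, gap 3.25 | Unadjusted, gap 2.0 | Group + gestational age |
|---|---|---|---|
| 0.05 | 13% | 8% | about 5% |
| 0.10 | 34% | 16% | about 5% |
| 0.15 | 60% | 29% | about 5% |

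With no gap or no slope, the unadjusted rate is 5%.

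**4. Cross-check in standardized units.** Let g be the gestational-age difference in SDs and r the within-group correlation of index and gestational age. The spurious standardized difference is r × g, and the noncentral t distribution at 40 versus 60 gives the rejection rate:

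| r | g = 0.5 | g = 1 | g = 1.5 |
|---|---|---|---|
| 0.2 | 8% | 16% | 31% |
| 0.3 | 11% | 31% | 59% |
| 0.5 | 23% | 68% | 95% |

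Regression on group and gestational age, simulated for r = 0.3 and 0.5, stayed at 4.5–5.2%.

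**5. Cost of adjustment.** In the week-based settings the standard error rises from 0.204 to 0.225 SD (gap 2.0) or 0.249 SD (gap 3.25): 0.225/0.204 = 1.10 and 0.249/0.204 = 1.22. In standardized units the factor is √(1 + 0.24 g²), where 0.24 = 0.4 × 0.6. This gives 1.03, 1.11 and 1.24 for g = 0.5, 1 and 1.5.

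**The case against.** A reader might infer that the primary comparison is an unadjusted test. The documents do not support that. No section designates a primary test, and the regression on group and gestational age is already planned for the indices that form the primary outcome. The Statistical Analysis section is generic text for all quantitative and qualitative data, and it does not cancel the regression. The abstract makes a second provision for gestational age. This objection stands, so the defect is an open choice and not a wrong primary analysis.

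A reader might also infer that no selection on gestational age took place. That goes too far as well. The article is condensed, and the flowchart, whose legend defines gestational week, is not shown. A procedure may exist elsewhere. What can be said is that the text at hand describes none.

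Nor does 40 versus 60 rule out all matching. Thirty IUGR or PE placentas could each be paired with 30 of the 40 normal ones, and variable-ratio matching exists. The conflict is only between the two sections' wording.

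The study is a pilot, described as exploratory, and the size of any bias cannot be known from the documents. Both points are fair, and they limit the weight of the figures. They do not settle which result carries the conclusion. An unseen analysis plan might rank the analyses, but it would not make the article's own statements agree.

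**Conclusion.** The point holds as one of reconciliation and hierarchy. The plan offers unadjusted tests, a gestational-age regression and comparisons within comparable gestational age, without saying which answers the primary objective. The two analysis sections disagree on matching, and the Discussion claims a control of gestational age that the described design does not deliver by itself.

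If the unadjusted result were used, a false disease effect would appear in about 8–60% of trials in the week-based settings, against about 5% for the adjusted model. These figures assume no disease effect, a linear gestational-age effect, earlier delivery in the pathological groups and two-sided 5% t tests. With no gap or no slope there is no excess; stronger correlations give more. The adjusted model holds 5% here partly because the simulated effect is linear, as the model assumes. The figures show a range, not a prediction for this trial.

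**What to change.** - **Statistical Analysis:** name the linear model from MR Image Analysis, with group and gestational age at delivery, as the primary analysis of each vascularization index. Report the adjusted group difference with its 95% confidence interval. Keep the t and Mann-Whitney tests as descriptive.
- **Matching:** either describe the matching procedure, or delete the matched option for group comparisons so that the section agrees with MR Image Analysis.
- **Discussion:** either describe how the groups were selected on gestational age, or say that the comparison is adjusted for gestational age.

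The model is already written and gestational age is already collected, so the change is one of wording. The price is precision: the standard error of the group difference rises by about 10–22% under the assumed gaps, and by less if the groups turn out closer in gestational age.
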